# Impact of preoperative patient education on prevention of postoperative complications after major visceral surgery: study protocol for a randomized controlled trial (PEDUCAT trial)

**DOI:** 10.1186/1745-6215-14-271

**Published:** 2013-08-26

**Keywords:** Patient education, Preoperative education, Postoperative complication, Prevention, Visceral surgery, Cluster randomization

## Abstract

**Background:**

In line with the growing number of surgical procedures being performed worldwide, postoperative complications are also increasing proportionately. Prevention of these postoperative complications is a high medical priority. Preoperative education of patients, including provision of preparatory information about the correct behavior after surgery, could improve the postoperative outcome, but the evidence for this is inconclusive. The aim of the PEDUCAT trial is to evaluate the feasibility and the impact of preoperative patient education on postoperative morbidity, mortality and quality of life in patients scheduled for elective major visceral surgery.

**Methods/design:**

PEDUCAT is designed as a cluster-randomized controlled pilot study. The experimental group will visit a standardized preoperative seminar to learn how best to behave after surgery in addition to being given a standard information brochure, whereas the control group will only receive the information brochure. Outcome measures such as postoperative morbidity, postoperative pain, postoperative anxiety and depression, patient satisfaction, quality of life, length of hospital stay and postoperative mortality will be evaluated. Statistical analysis will be based on the intention-to-treat population. Analysis of covariance will be applied for the intervention group comparison, adjusting for age, center and quality of life before surgery. This is a pilot study to show the feasibility of the concept. Nevertheless, the planned sample size of n = 204 is large enough to show an effect with power of 90% and a significance level of 5%.

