### Sample size

A total of 300 patients (50 clusters) will be randomized and screened for eligibility. The number of patients meeting the inclusion criteria will be 204 (34 clusters). One hundred and two patients (17 clusters) per group will be analyzed (see Figure 1).

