### Type of trial

The PEDUCAT trial is a single-center, explorative, cluster-randomized, controlled surgical pilot study with two parallel study groups.

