### Recruitment and trial timeline

The estimated time frame for randomization of 204 eligible patients is 34 weeks. The total duration of the trial is expected to be 13 months, including analysis. Recruitment of participants started in October 2012 as a single-center trial. Patients are followed up for 30 days after surgery. The actual overall duration or recruitment time may differ.

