### Randomization

Two wards of the Department of General, Visceral and Transplantation Surgery, University of Heidelberg, each with 36 beds, are participating in the trial. The patients are all comparable with regard to their diagnosis, planned surgery and baseline data. Patients admitted from Monday to Wednesday on each of the two wards are defined as a cluster. There will be two clusters per week. In order to prevent selection bias and to achieve comparable groups for known and unknown risk factors, randomization will be performed on a block basis with 1:1 allocation. Subjects are assigned to either group A or group B based on a computer-generated randomization list prepared by the Institute of Medical Biometry and Informatics, University of Heidelberg, Germany. The randomization list is in the charge of an independent member of staff of the Clinical Study Center Surgery, Department of General, Visceral and Transplantation Surgery, University of Heidelberg who discloses the randomization of the two wards every second week. The investigators are informed, and the wards are updated about the randomization result.

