## Statistical methods

### Sample size calculation

This is a pilot study. Therefore, no sample size calculation was performed. A sample size of 102 patients per study group seems sufficient to test the feasibility of patient recruitment and cluster randomization, assuming a cluster size of six patients.

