### Statistical analysis

All endpoints will be analyzed descriptively by tabulation of the measures of the empirical distributions. Depending on the scale level of the variables, means, standard deviations, medians, and first and third quartiles, as well as either minimum and maximum or absolute and relative frequency, will be reported. Additionally, Kaplan-Meier analysis will be performed for postoperative mortality. Descriptive *P*-values of the corresponding statistical tests comparing the treatment groups will be given, together with the associated 95% confidence intervals. Because of the cluster randomization, the analyses will involve a multilevel regression approach with patients at level one and education cluster at level two. When appropriate, graphical methods will be used to visualize the findings. The homogeneity of the treatment groups will be described by comparison of the demographic data and the baseline values.

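### The abstract and the Statistical analysis section name different models for the same group comparison, and the abstract adjusts for center in a single-center trial

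*Protocol article*

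**What the plan says.** The abstract (Methods/design) describes the comparison of the two groups in one sentence: "Analysis of covariance will be applied for the intervention group comparison, adjusting for age, center and quality of life before surgery". It calls the trial cluster-randomized, but mentions no cluster effect in the analysis.

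The section Statistical analysis describes it differently: "Because of the cluster randomization, the analyses will involve a multilevel regression approach with patients at level one and education cluster at level two". It does not mention analysis of covariance, and age, center and baseline quality of life do not appear there. It calls the P-values descriptive and promises 95% confidence intervals with them.

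On the number of centers, the section Type of trial states: "The PEDUCAT trial is a single-center, explorative, cluster-randomized, controlled surgical pilot study with two parallel study groups". The section Recruitment and trial timeline agrees: "Recruitment of participants started in October 2012 as a single-center trial". The eligibility section names one department at one university hospital.

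The randomized unit is defined under Randomization: "Patients admitted from Monday to Wednesday on each of the two wards are defined as a cluster". There are two wards, so two clusters arise per week.

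**The concern.** An abstract may leave out detail. This one names a different method, with covariates that the body never mentions. A reader cannot tell whether the treatment effect will come from a patient-level ANCOVA, from a multilevel model without covariates, or from a multilevel model that includes those covariates. Both statements are current text in the same article, so a more detailed plan elsewhere would not make them agree.

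Two things are at stake. First, patients admitted to the same ward in the same week share an allocation and may have correlated outcomes. A patient-level ANCOVA treats them as independent, so its standard error is too small whenever the ICC is above zero. Second, leaving open whether clustering is modeled leaves room to choose after the data have been seen.

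The covariate center is a separate fault. A factor with one level is collinear with the intercept, so it drops out of the model and adjusts for nothing. It does not affect the standard error either way. It does show that the abstract sentence was not matched to this design.

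**Working it through.** **Inputs from the protocol article**

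- Cluster size m = 6. Sample size calculation: "assuming a cluster size of six patients".
- Patients and clusters per arm. Sample size: "One hundred and two patients (17 clusters) per group will be analyzed".
- Check of the plan's own counts: 17 × 6 = 102 per arm and 34 × 6 = 204 in total. Both agree with the text.

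**Input not in the article**

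- No ICC is given. It is assumed here and shown as a range from 0.01 to 0.10. The relevant ICC is the one that remains after covariate adjustment.

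**Formulas** (continuous outcome, equal clusters, two-sided nominal 5%)

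- Design effect: DE = 1 + (m − 1) × ICC = 1 + 5 × ICC.
- Correct SE divided by the SE from a model without a cluster term: √DE.
- Actual type I error of that model: 2 × (1 − Φ(1.96/√DE)).

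**Results**

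| Assumed ICC | DE | Correct SE / reported SE | 1.96/√DE | Type I error |
|---|---|---|---|---|
| 0 | 1.00 | 1.000 | 1.960 | 5.0% |
| 0.01 | 1.05 | 1.025 | 1.913 | 5.6% |
| 0.05 | 1.25 | 1.118 | 1.753 | 8.0% |
| 0.10 | 1.50 | 1.225 | 1.600 | 11.0% |

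Equivalently, the reported SE is too small by 1 − 1/√DE, which is 2.4%, 10.6% and 18.4% for ICC 0.01, 0.05 and 0.10. A nominal 95% confidence interval then covers about 94.4%, 92.0% and 89.0% of the time (100% minus the type I error).

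**Check by simulation** (34 clusters of six, no true effect, 10,000 runs per ICC). A patient-level t-test rejected in 5.1%, 6.1%, 7.4% and 11.2% of runs at ICC 0, 0.02, 0.05 and 0.10. A t-test on the cluster means rejected in 4.8% to 5.5%. So the excess comes from the missing cluster term, and an analysis that respects the clusters removes it.

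**The case against.** The strongest reply is that the detailed section already handles clustering and says why. Abstracts condense, and age and baseline quality of life could be fixed effects inside the multilevel model. The trial is an exploratory pilot with descriptive P-values, so a raised type I error matters less than in a confirmatory trial. At an ICC near 0.01 the error is negligible, and the figures apply only to continuous outcomes: ANCOVA is not a natural analysis for complications or mortality.

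Most of this stands, and it limits the severity. It does not remove the contradiction. Neither place says that the covariates belong in the multilevel model, and none of it accounts for center. Interval width also matters in a pilot, since the article promises 95% confidence intervals.

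A reader might infer three stronger points, none of which the article supports:

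- *The trial's analysis will ignore clustering.* The abstract omits a cluster term but does not say that patients are treated as independent, and the detailed section specifies a model that respects the clusters.
- *The level-two unit named in "the analyses will involve a multilevel regression approach with patients at level one and education cluster at level two" excludes controls, who attend no seminar.* Clusters are defined by ward and admission days before any education takes place, and 17 are counted in each group. At most the term is loose wording.
- *Leaving ward out of the model biases the result.* With a random intercept for the ward-by-week cluster, differences between wards enter the between-cluster variance. That costs precision, not validity. Uneven spread of the arms over the wards would be chance imbalance.

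**Conclusion.** The point holds in this form: the abstract and the Statistical analysis section state different models for one comparison, and the abstract's covariate list contains a factor that cannot exist in this trial. Both follow from the text without any assumption.

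The numerical consequence is conditional. It arises only if the abstract's ANCOVA is run without a cluster term, only for an ICC above zero, and as computed only for continuous outcomes in clusters of about six. It is trivial at an ICC of 0.01 and becomes material from about 0.05, up to a standard error that should be 22% larger at 0.10. The ICC values are assumptions. If the Statistical analysis section governs, this harm does not occur.

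Severity: should be fixed. It is a contradiction that is cheap to remove, not a demonstrated flaw in the analysis that will be run.

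**What to change.** Replace the abstract's ANCOVA sentence with the model of the Statistical analysis section, and describe that model identically in both places:

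- a random intercept for the randomized ward-by-week cluster, in both arms;
- fixed effects for arm, age and baseline quality of life;
- center deleted, or replaced by ward, which does vary.

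Including ward is optional. It may improve precision and costs one degree of freedom: with 34 clusters and two arms, a cluster-level comparison has 34 − 2 = 32 degrees of freedom, and ward reduces this to 31. Ward should already be known for every patient, because it is part of the cluster definition.

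The cost is a change of wording, with no additional data collection and no change to the design. It should be made before the group comparison is run, so that the choice of model cannot depend on the results.

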In summary, providing preoperative education might improve patients’ understanding and greatly alleviate their anxieties and fears with regard to the surgical experience, helping them to remain calm and face the situation in a positive way. In a review published in 1998, however, Shuldham showed that most of the studies conducted from the 1950s to the 1980s did not meet today’s methodological standards for clinical studies owing to lack of blinding, unclear randomization protocols, lack of sample homogeneity and insufficient sample size [8]. Frequently, heterogeneous groups of patients undergoing various types of operations were used. However, indices such as pain may vary widely depending upon the surgical procedure. In a second review, Shuldham found no demonstrable benefit from preoperative teaching of the patient having coronary artery bypass surgery and further research was suggested [9]. In a randomized controlled trial led by the same author, patients with bypass surgery were again investigated. No significant impact of patient education on anxiety, pain or depression was found. However, the length of hospital stay differed significantly in the patients who were given additional presurgical information. Shuldham *et al*. concluded that their results demonstrated that no significant benefit was to be gained from preoperative education [10].

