	• total peripheral white blood cell (WBC) count > 12 g/L or WBC < 4.5 g/L or > 15% immature neutrophils (bands), regardless of total peripheral WBC count
	• increased plasma or serum C-reactive protein (CRP) level as shown by a level of at least twice the upper limit of the hospital normal range
	and
	chest X-ray or CT scan findings (anterior-posterior (ap) or posterior-anterior (pa) and, if possible, lateral views) in agreement with the clinical diagnosis of bacterial pneumonia, that is, the appearance of new, progressive pulmonary infiltrate(s) attributable to infectious etiology
2. Deep vein thrombosis	clinical evidence (for example, painful, swollen, warm, livid leg) of a previously unknown thrombosis located in a deep leg or pelvic vein with radiological confirmation by duplex sonography or CT-angiography
3. Pulmonary embolism	clinical suspicion of pulmonary embolism (for example, tachycardia, dyspnea) confirmed by spiral CT or lung perfusion scintigraphy
4. Burst abdomen	postoperative absence of continuity of the abdominal fascia in combination with wound dehiscence requiring reintervention
5. Falls	in-hospital falls

The frequency and type of postoperative complications will be evaluated on days 2, 7 and 30 after surgery. Postoperative pain will be documented at baseline and on days 2 and 7 after surgery with a modified validated version of the BPI. Perioperative anxiety and depression will be investigated with the HADS questionnaire at baseline and on days 7 and 30 after operation. Quality of life will be assessed using the SF-12 questionnaire at baseline and at 30 days postoperatively. Additionally, the length of hospital stay and the postoperative mortality will be evaluated (Table 3).

**Table 3 T3:** Study visits of the PEDUCAT trial

**Documentation**	**Visit 1**	**Visit 2**	**Visit 3**	**Visit 4**	**Visit 5**
	**Screening**	**2 days after surgery**	**7 days after surgery**	**30 days after surgery**	**End of study**
Baseline data, demographics	X				
Eligibility criteria	X				
Randomization	X				
Assessment of complications and safety		X	X	X	X
Morbidity, mortality, length of stay		X	X	X	X
Postoperative pain (BPI)	X	X	X		
Perioperative anxiety and depression (HADS)	X		X	X	
Patient satisfaction			X		
Quality of life (SF-12)	X			X	

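### The only covariate list the protocol names omits baseline BPI and baseline HADS, although both are collected at Visit 1; only SF-12 is given its own baseline

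*Protocol article*

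**What the plan says.** The Methods/design part of the abstract lists the outcomes and then gives one adjusted model, an analysis of covariance for the group comparison, "adjusting for age, center and quality of life before surgery". The Statistical analysis section specifies a different framework and names no covariates: "the analyses will involve a multilevel regression approach with patients at level one and education cluster at level two". It adds "Descriptive *P*-values of the corresponding statistical tests comparing the treatment groups will be given", with 95% confidence intervals.

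Under Outcomes, "Postoperative pain will be documented at baseline and on days 2 and 7 after surgery" and "Perioperative anxiety and depression will be investigated with the HADS questionnaire at baseline and on days 7 and 30 after operation". Table 3 confirms that BPI, HADS and SF-12 are all completed at Visit 1. SF-12 is repeated at 30 days.

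The Type of trial section describes a single-center pilot. Under Preliminary data, earlier studies are criticised for mixing operations because "indices such as pain may vary widely depending upon the surgical procedure". The eligibility section of this trial admits multivisceral, pancreatic, gastric, esophageal, hepatic and rectal procedures.

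**The concern.** For a scale measured before and after surgery, the patient's own starting value is usually the strongest baseline predictor available. The named list uses this for quality of life and not for pain, anxiety or depression. Baseline quality of life stands in for these scales only as far as it correlates with them.

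Two things are at stake. The confidence intervals for BPI and HADS may be wider than the collected data require. With 17 clusters per arm, a chance difference in baseline pain or anxiety would also stay uncorrected in the estimate. One of the three named covariates, center, is a constant and adjusts for nothing. The list therefore needs editing in any case.

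**Working it through.** **Inputs from the article.** 102 patients and 17 clusters per group (Sample size); cluster size 6 (Sample size calculation); 17 × 6 = 102 and 34 × 6 = 204, as stated. The abstract claims 90% power at 5% significance. That claim cannot be reproduced: no effect size, standard deviation or intracluster correlation (ICC) is given, and the Sample size calculation section says no calculation was done.

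**Assumed inputs.** The article gives no correlations. Let ro be the correlation of the outcome with its own baseline, rq its correlation with baseline quality of life, and c the correlation between the two baselines, taken as 0.5.

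**Step 1: gain beyond baseline quality of life.** Residual variance with quality of life alone is 1 − rq². With both baselines it is 1 − R², where R² = (ro² + rq² − 2·ro·rq·c)/(1 − c²). For ro = 0.5 and rq = 0.2, R² = (0.25 + 0.04 − 0.10)/0.75 = 0.253. The ratio is 0.747/0.96 = 0.778, a fall of 22%, and 204/0.778 ≈ 262 patients.

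| ro | rq | R² | Variance ratio | Fall | 204 / ratio |
|---|---|---|---|---|---|
| 0.2 | 0.2 | 0.053 | 0.986 | 1% | 207 |
| 0.2 | 0.4 | 0.160 | 1.000 | 0% | 204 |
| 0.3 | 0.2 | 0.093 | 0.944 | 6% | 216 |
| 0.3 | 0.4 | 0.173 | 0.984 | 2% | 207 |
| 0.5 | 0.2 | 0.253 | 0.778 | 22% | 262 |
| 0.5 | 0.4 | 0.280 | 0.857 | 14% | 238 |
| 0.7 | 0.2 | 0.520 | 0.500 | 50% | 408 |
| 0.7 | 0.4 | 0.493 | 0.603 | 40% | 338 |

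With c = 0.3 instead, the falls for rq = 0.2 and 0.4 are 7% and 4% at ro = 0.3, and 22% and 19% at ro = 0.5.

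**Step 2: detectable difference.** At 90% power and two-sided 5% without clustering it is (1.960 + 1.282) × √(2/102) = 0.454 SD. At an assumed ICC of 0.05 the design effect is 1 + 5 × 0.05 = 1.25, which gives 0.454 × √1.25 = 0.507 SD. With quality of life alone (rq = 0.2) this becomes 0.507 × √0.96 ≈ 0.50 SD. With the own baseline added (ro = 0.5) it is 0.507 × √0.747 ≈ 0.44 SD. This assumes that adjustment reduces the variance within and between clusters in the same proportion.

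**Step 3: chance imbalance.** If a baseline score also has ICC 0.05, the group difference has standard error √(2/102 × 1.25) = 0.157 SD. A gap above 0.2 SD in either direction then arises in about 20% of trials (0.2/0.157 = 1.28). At ro = 0.5 such a gap moves an estimate with no baseline adjustment by 0.5 × 0.2 = 0.1 SD. Adjusting for quality of life removes part of this.

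**Procedure type.** The article gives no between-procedure variance, so no gain can be computed.

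**The case against.** The strongest reply is that one sentence in an abstract is not a full specification. The Statistical analysis section names no covariates, and a full protocol or analysis plan may set them by outcome. That stands in part: those documents may already do what is asked here. The abstract nevertheless states a choice, and that choice leaves out two baselines that are collected.

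Four stronger readings are tempting and not supported:

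- A reader might infer that every outcome is adjusted for quality of life instead of its own baseline. The abstract speaks only of the group comparison. SF-12 does receive its own baseline. Complications, mortality, length of stay and satisfaction have no baseline value in Table 3. The point concerns BPI and HADS.
- A reader might infer that these baselines serve only to describe homogeneity. The Statistical analysis section gives them that use but does not say it is the only one.
- A reader might take 1 − ro² as the saving: 9%, 25% and 36% at 0.3, 0.5 and 0.6, or 204/0.75 = 272 patients at 0.5. That compares with no baseline covariate, whereas quality of life is already in the list. The smaller figures in the table are the relevant ones.
- A reader might conclude that the comparison is biased. Omitting a prognostic covariate does not bias a randomized comparison on average.

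It is also fair to say that preoperative pain may predict postoperative pain only weakly, and that the trial is an explorative pilot with descriptive P-values. Both limit the consequence. The article still promises 95% confidence intervals, and their width is what this affects. On procedure type, the Randomization section asserts that patients are comparable in planned surgery. The eligibility list and the Preliminary data section give some reason to doubt this, but the grouping is debatable and the gain unknown.

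**Conclusion.** The point holds for BPI and HADS. The named covariate list omits their collected baselines and includes a center term that is constant.

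Under the assumptions shown, the loss of precision ranges from nil, when the own baseline is a weak predictor, through 2% to 6% of residual variance at an own-baseline correlation of 0.3, to 14% to 22% at 0.5. For ICC 0.05 and correlations of 0.5 (own baseline) and 0.2 (quality of life), the detectable difference at 90% power falls from about 0.50 to 0.44 SD. Every correlation and the ICC are assumptions.

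The consequence is lower precision and uncorrected chance imbalance, not average bias. Because the remedy is nearly free, the change should be made. Adjustment for procedure is a matter to consider and not part of what has been shown.

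**What to change.** State the covariates by outcome in the Statistical analysis section, inside the multilevel model, and bring the abstract's sentence into line:

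- postoperative BPI scores: the corresponding baseline BPI score;
- HADS-anxiety and HADS-depression: each its own baseline;
- 30-day SF-12 scores: the corresponding baseline SF-12 score;
- keep age and drop center.

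Consider a coarse planned-procedure factor for pain, with its groups defined before the data are analyzed.

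The cost is mainly wording, since the baselines are already collected. The adjustment uses a few degrees of freedom, more if a procedure factor is added. Patients without a baseline questionnaire need a stated rule so that they are not dropped. The sponsor should also confirm that the Visit 1 questionnaires are completed before the patient learns the group, since wards are told their allocation in advance. If they are not, securing that order is a small operational change.

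### The abstract claims 90% power for n = 204, but the Methods say no sample size calculation was done and the article gives no inputs for one

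*Protocol article*

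**What the plan says.** Two places in the protocol article deal with the adequacy of the sample size.

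- **Abstract, Methods/design.** After noting that the trial is a pilot meant to show feasibility, the abstract sets that caveat aside and adds that "n = 204 is large enough to show an effect with power of 90% and a significance level of 5" per cent. It does not say which outcome, which effect, or whether the test is one- or two-sided.
- **Statistical methods, Sample size calculation.** "This is a pilot study. Therefore, no sample size calculation was performed". The number is then justified differently: "A sample size of 102 patients per study group seems sufficient to test the feasibility of patient recruitment and cluster randomization". Each cluster is taken to hold six patients.

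The rest of the article agrees with the second statement. Type of trial describes a "single-center, explorative, cluster-randomized, controlled surgical pilot study". Statistical analysis plans descriptive P-values with 95% confidence intervals from a multilevel model with patients nested in education clusters. Outcomes lists seven domains (morbidity, pain, anxiety and depression, satisfaction, quality of life, length of stay, mortality) and ranks none of them.

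**The concern.** A power figure is the result of a calculation for a named endpoint, a named effect, an assumed variance or event rate and, in a cluster trial, an assumed ICC. The article says no such calculation was made and supplies none of these inputs. If a calculation was done, the Methods section is wrong. If none was done, the abstract's figure has no source.

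What is at stake is interpretation. The claim sits in the abstract, next to aims that include morbidity, mortality and quality of life. A reader who meets only the abstract could take a null result on any of these as evidence of no effect from a well-powered trial. The same reader could take one small P-value among several unranked outcomes as the effect the trial was sized to show. The design as described in the body supports neither reading.

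**Working it through.** **Inputs from the article.** 204 patients in total; 102 patients and 17 clusters per group (Sample size); cluster size six (Sample size calculation); 1:1 allocation (Randomization); power 90% and significance level 5% (abstract). The counts agree: 34 × 6 = 204 and 17 × 6 = 102.

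**Inputs the article does not give.** Endpoint, effect size, standard deviation or event rates, ICC and sidedness. The values below are therefore assumptions: ICC 0, 0.05 and 0.10; two-sided 5%; no covariate adjustment.

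**Step 1: can the 90% be reproduced?** No. Without an effect and a variance there is nothing to enter. One can only work backwards to the effect for which the design would have 90% power.

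**Step 2: detectable standardised difference, normal approximation.** Design effect DE = 1 + (6 − 1) × ICC, and d = (1.960 + 1.282) × √(2 × DE / 102).

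- ICC 0: DE = 1.00, d = 3.242 × √(2/102) = 0.454
- ICC 0.05: DE = 1.25, d = 3.242 × √(2.5/102) = 0.507
- ICC 0.10: DE = 1.50, d = 3.242 × √(3/102) = 0.556

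**Step 3: the same with 34 clusters.** The group comparison has 34 − 2 = 32 degrees of freedom at cluster level, so a noncentral t distribution is the better reference. The noncentrality parameter is d × √(102 / (2 × DE)).

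| Assumed ICC | d needed for 90% power, t(32) | Power for d = 0.4, t(32) |
|---|---|---|
| 0 | 0.468 | 79% |
| 0.05 | 0.523 | 70% |
| 0.10 | 0.573 | 62% |

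**Step 4: one binary illustration.** Assume a control risk of 10% that is halved to 5%, and use the two-proportion formula with pooled variance under the null. The mean risk is 0.075.

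- Null term: 1.960 × √(2 × 0.075 × 0.925) = 0.730
- Alternative term: √(0.10 × 0.90 + 0.05 × 0.95) = 0.371
- ICC 0 (n = 102): z = (0.05 × √102 − 0.730) / 0.371 = −0.61, power about 27%
- ICC 0.05 (n = 102/1.25 = 81.6): z = (0.05 × √81.6 − 0.730) / 0.371 = −0.75, power about 23%

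The attainable power therefore depends on the outcome, the effect and the ICC. A single 90% for an unspecified effect describes none of them.

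**The case against.** **The 90% may be true of something.** This stands. Without clustering, a standardised difference of about 0.45 gives 90% power by the normal approximation. A reader might infer from the contradiction that the figure is numerically wrong. The article does not allow that conclusion, because no sum in it is shown to be false.

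**A journal article condenses the full protocol.** This would excuse missing details of a calculation. It does not apply here, because the article does not defer the calculation elsewhere but says that none was performed.

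**The abstract may have a continuous outcome in mind.** The power sentence follows closely on an analysis of covariance adjusted for, among other things, baseline quality of life. That fits a continuous outcome at least as well as rare complications, and such an adjustment would improve power. With an assumed baseline-outcome correlation of 0.5, the normal-approximation range of 0.454 to 0.556 shrinks by √(1 − 0.25) = 0.866 to about 0.39 to 0.48. The objection shows that the range in the table depends on its assumptions. It does not supply the missing endpoint or effect.

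**Rare-event arguments go beyond the article.** A reader might take seven million complications in 234 million operations (3.0%) from the Background as the trial's event rate and conclude that power is close to nil. The Background gives seven million as a worldwide minimum over all major surgery, and Preliminary data expects a higher incidence after the procedures studied here. A reader might also treat the complications and mortality as the main outcomes and call the effects needed for 90% power implausible. The article ranks no outcome and gives no control rate against which plausibility could be judged.

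**The body already guards against misreading.** Largely true: the exploratory label, the feasibility basis and the descriptive P-values are all there. The abstract sentence nevertheless overrides the pilot caveat in the part of the article that is read most.

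**Conclusion.** The abstract's power claim and the Methods section cannot both stand, and the article contains no basis for the 90%. The figure is unsupported rather than refuted.

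As an indication of size only, 90% power needs a standardised difference of about 0.47 to 0.57. This holds for 17 clusters of six per arm, two-sided 5%, t(32), no covariate adjustment and assumed ICCs of 0 to 0.10. The 10% risk and the ICCs in the binary example are likewise assumptions; its 23 to 27% shows only that the 90% cannot be read as covering every outcome.

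The fault lies in one sentence. It affects how results will be read, not randomization, data collection or analysis. It should be corrected because it is wrong as written and the correction is simple.

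**What to change.** Delete the power sentence from the abstract and put in its place, for example: *No formal sample size calculation was performed. The number of patients was chosen to assess the feasibility of recruitment and cluster randomization. Between-group results are exploratory estimates with 95% confidence intervals.*

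Alternatively, if a calculation does lie behind the 90%, state the endpoint, effect, standard deviation or event rates, ICC and sidedness, and correct the section Sample size calculation so that it no longer says none was done.

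A statement of what the design could detect is optional. If one is wanted, it should be labelled as resting on assumed ICCs and no covariate adjustment, and should use the t(32) values: about 0.47 (ICC 0), 0.52 (ICC 0.05) or 0.57 (ICC 0.10) for 90% power at two-sided 5%.

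The cost is wording only. The loss is a reassuring figure that the article cannot support.
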